### **9.2.3 Recording and Reporting of Adverse Events**

AE reporting and data management will be performed according to the following relevant guidelines:

- Directive 2001/20/EC (European Clinical Trial Directive)
- Committee for Proprietary Medicinal Products (CPMP)/ICH/E2A/377/95 (Clinical Safety Data Management: Definition and Standards for Expedited Reporting)
- CPMP/ICH/135/95 (GCP)
- 21 Code of Federal Regulations (CFR) 312.32 (FDA).

#### **9.2.4 Recording of AEs/SAEs**

All SAEs must be reported on the SAE form in the eCRF.

All SAEs that occur after the participant has signed the ICF up to 30 days after the last administration of the last investigational product will be reported. All non-serious AEs that are possibly related to the study are collected from randomization until 30 days after the last visit (at 24 weeks). All SAEs must be reported on the SAE form in the eCRF.

NCI CTCAE (National Cancer Institute; Common Terminology Criteria for Adverse Events) grading is used in haem/onc and refers to mild (G1) moderate (G2), severe (G3), life-threatening (G4), or dead (G5); currently v5.0 is used.

Participants with an AE of Grade > 1 will be further followed until the resolution of the AE to CTCAE Grade 0-1 or until initiation of a new therapy, whichever occurs first.

Participants with an adverse drug reaction (ADR) ongoing at EAPV must be followed until the ADR resolves, becomes stable, or is considered not clinically significant by the investigator.

A Data Safety Monitoring Board (DSMB) will be established to assess safety data, monitor trial integrity and make recommendations to the Sponsor.

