#### *Pre- and probiotics*

*Anaerobutyricum soehngenii* and *Bifidobacterium animalis*, subsp. *lactis* are commensal inhabitants of the human intestine, and safe to administer. Pasteurized *A. muciniphila* is a pasteurized form of another commensal of the gut, and safe to administer in humans. The combination of these 3 bacteria is not well studied, although we expect no negative effect of interbacterial actions.

Fructo-oligosaccharides are indigestible prebiotics, which are safe and over-the-counter available.

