### **9.2 AEs, and SAEs**

#### **9.2.1 Adverse events (AEs)**

Adverse events are defined as any undesirable experience occurring to a individual during the study, whether or not considered related to [the investigational product / trial procedure/ the experimental intervention].

An event that is part of the natural course of the disease under study is captured in the study as a clinical activity measure. However, any specific symptoms or sequelae of the disease evolution (e.g., organ failure, respiratory distress) will be considered AEs. Clinically significant changes in laboratory values, blood pressure and pulse will not necessarily be reported as AEs. However, abnormal AEs that constitute an SAE or lead to discontinuation of administration of study drug must be reported and recorded as an AE.

The investigator is responsible for reviewing laboratory test results and determining whether an abnormal value in an individual study subject represents a change from values before the study. In general, abnormal laboratory findings without clinical significance (based on the Investigator's judgment) should not be recorded as AEs; however, laboratory value changes requiring therapy or adjustment in prior therapy should be considered AEs.

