#### **9.2.2 Serious adverse events (SAEs)**

A serious adverse event is any untoward medical occurrence or effect that

- results in death;
- is life threatening (at the time of the event);
- requires hospitalisation or prolongation of existing inpatients' hospitalisation;
- results in persistent or significant disability or incapacity;

- is a congenital anomaly or birth defect; or
- any other important medical event that did not result in any of the outcomes listed above due to medical or surgical intervention but could have been based upon appropriate judgement by the investigator.

An elective hospital admission will not be considered as a serious adverse event.

A hospitalization meeting the regulatory definition for “serious” is any inpatient admission, regardless of the length of stay, even if as a precautionary measure for continued observation. Elective hospitalizations for the routine administration of protocol therapy, therapeutic blood products, treatment of a pre-existing condition that did not worsen from baseline, elective procedures, or for social or technical reasons are not considered SAEs. However, prolongation of hospitalization or re-admission after the individual has been discharged for reasons other than administrative, will be considered SAEs.

All SAEs that occur after any participant has been enrolled (i.e. who signed ICF), before treatment, during treatment, or within 30 days following the cessation of treatment, whether or not they are related to the study, must be recorded.

The investigator will report all SAEs to the sponsor without undue delay after obtaining knowledge of the events, except for the following SAEs:

The sponsor will report the SAEs through the web portal *ToetsingOnline* to the accredited METC that approved the protocol, within 7 days of first knowledge for SAEs that result in death or are life threatening followed by a period of maximum of 8 days to complete the initial preliminary report. All other SAEs will be reported within a period of maximum 15 days after the sponsor has first knowledge of the serious adverse events.

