### **9.3 Follow-up of adverse events**

All AEs will be followed until they have abated, or until a stable situation has been reached.

Depending on the event, follow up may require additional tests or medical procedures as indicated, and/or referral to the general physician or a medical specialist.

SAEs need to be reported till end of study within the Netherlands, as defined in the protocol.

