## **14. Amendments**

### **14.1 First amendment**

The changes of the protocol in the first amendment are:

1. The delayed release '(DR) capsules will be replaced with 'next generation enteric' (NGE) capsules.
2. A questionnaire to screen donors is added to the accessory documents.
3. The dates of the study visits (week 0, 8, 16 and 24) are changed into a range of 6 days each.
4. The screening of fecal donors is changed to a step by step procedure.
5. A procedure to deblind is added to the protocol.
6. The erroneous use of 'duodenal tube' is corrected to 'LFMT capsules', conform the rest of the protocol.
7. The label of the LFMT capsules in the protocol is changed.
8. Not all non-serious AEs, but only non-serious AEs that possibly are related to the study are reported.
9. The erroneous 6 months interval of donor screening is corrected to 3 months in the protocol.

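### Non-serious adverse events get an AE entry only if first judged possibly related to the study, which conflicts with the rule in 9.2.1 on events leading to discontinuation and makes the by-arm safety summary depend on attribution

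*Protocol*

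**What the plan says.** Protocol section 9.2.4 sets the collection rule for non-serious events: "All non-serious AEs that are possibly related to the study are collected from randomization until 30 days after the last visit". The list of changes in section 14.1, item 8, agrees with it: "Not all non-serious AEs, but only non-serious AEs that possibly are related to the study are reported". The restriction is therefore a decision and not a slip.

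Other parts of chapter 9 carry no relatedness condition:

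- Section 9.2.1 defines an AE as "any undesirable experience occurring to a individual during the study, whether or not considered related" to the product or procedure. It then adds that "abnormal AEs that constitute an SAE or lead to discontinuation of administration of study drug must be reported and recorded as an AE".
- Section 9.2.2 requires SAEs to be captured "whether or not they are related to the study, must be recorded".
- Section 9.2.4 itself follows participants with any AE above Grade 1 until it falls to Grade 0–1 or a new therapy starts.
- Section 9.3 says: "All AEs will be followed until they have abated, or until a stable situation has been reached".

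Section 9.2.5 has the investigator class each AE as possibly or probably related, or as not related. The reference there is the study medication, whereas the filter in 9.2.4 refers to the study.

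**The concern.** A relatedness judgement is normally a property of a recorded event. Here it decides whether a non-serious event is recorded as an AE at all. What is excluded at entry cannot be tabulated by arm later, and no analysis plan can bring it back.

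The design makes individual attribution difficult. Both arms take three bacterial products and FOS daily, and section 6.5 concedes of the bacteria that "The combination of these 3 bacteria is not well studied". The symptoms the protocol expects from LFMT (sections 6.4 and 6.5) and from FOS (section 7.3) overlap, abdominal pain and flatulence being examples. Randomisation against placebo capsules can separate an LFMT effect from this background without anyone judging single cases, but only if events are counted in both arms regardless of attribution.

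At stake are the descriptive safety summary by arm and the material that reaches the DSMB, whose main focus under section 9.4 is participant safety. Sections 11.3 and 13 also make claims about few or negligible adverse effects, and a pre-filtered set of events is a weak basis for these.

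**Working it through.** **Text check.** The plan gives no figure on this point to reproduce, so the passages are set against the filter in 9.2.4 one by one.

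1. *9.2.1, definition.* A definition can be wider than a collection rule. This is a difference of scope and not a contradiction.
2. *9.2.1, events leading to discontinuation.* Take a non-serious AE that stops study drug and is judged unrelated. Section 9.2.1 says it must be recorded as an AE; section 9.2.4 does not collect it. Both rules cannot be followed. The sentence comes straight after one on laboratory, blood pressure and pulse changes, so it might be read as covering only abnormal findings of that kind. The conflict then covers fewer events but remains, because there is still no relatedness condition. The case is realistic: section 8.4.1 withdraws participants whose new condition requires a change in drug prescriptions.
3. *9.3 and the Grade > 1 rule in 9.2.4.* Both require follow-up without regard to relatedness. An event with no AE entry has nothing against which follow-up can be documented. They fit only if silently read as applying to collected AEs.
4. *9.2.5.* The filter asks about the study, the classification about study medication. An event attributed to the liver biopsy could pass the first and be unrelated under the second. The not-related class is not empty, because SAEs are recorded whatever their cause, but it should hold almost no non-serious events.
5. *9.2.2.* SAEs are fully captured, so the point is confined to non-serious events.

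**Size, as an illustration only.** The protocol gives neither AE rates nor the share of events that would be called possibly related. Inputs:

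- n = 24 per arm (section 4.4).
- Assumed true proportions with an event: 40% vs 20%.
- Assumed share s passing the filter, equal in both arms because the judgement is blinded (section 8.2).
- One event per participant, so the observed proportion is the true proportion times s.

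The test is z = (a/n − b/n) / √[p̄(1 − p̄)(2/n)], with a and b the numbers of participants with an event and p̄ = (a + b)/(2n). Power is the sum of binomial probabilities over all pairs (a, b) with |z| > 1.96 (two-sided 5%).

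| Share passing, s | Observed proportions | Difference | Power |
|---|---|---|---|
| 100% | 40% vs 20% | 20 points | 33% |
| 90% | 36% vs 18% | 18 points | 30% |
| 80% | 32% vs 16% | 16 points | 26% |
| 50% | 20% vs 10% | 10 points | 17% |

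With equal s the ratio between arms stays at 2, while the absolute difference shrinks in proportion to s.

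Unequal attribution would be a different matter. With equal true rates of 30%, and 80% vs 40% of events called related, the recorded rates would be 0.30 × 0.80 = 24% and 0.30 × 0.40 = 12%. That needs attribution to differ strongly by arm.

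**The case against.** The restriction was introduced openly by amendment, and limiting low-grade safety data is a choice a sponsor may make. The filter is also wide. Section 9.2.5 counts an event as possibly related when timing is reasonable even if another cause may explain it, and with daily dosing for 24 weeks timing will seldom rule an event out. Gastrointestinal symptoms are listed as known effects, so they are the likeliest to pass, and doubt favours inclusion. SAEs are complete. No AE outcome appears in sections 8.1.2 and 8.1.3, and section 10 states no AE test. Safety blood is drawn at weeks 8 and 16 (section 8.3), and changes in health status are documented (section 3), so an excluded event may leave a trace elsewhere. Finally, 33% power is low even without any filter.

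Most of this stands, and it limits the size of the point. It makes 80–90% retention more plausible than 50%. It does not resolve the conflict over events leading to discontinuation, and a trace in a health-status note is not a graded, tabulated AE.

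Two stronger readings are tempting. A reader might infer that the safety comparison is biased, because section 6.9 has the executing researchers make and dispense the capsules. But the protocol does not say that they know the allocation or that they judge causality; the trial is described as double blind, and section 9.1 gives deblinding to researchers independent of the study. A reader might also infer that 9.2.4 contradicts the AE definition as such. It does not, for the reason given under the first step of the text check.

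**Conclusion.** The point holds in a limited form. One pair of rules cannot both be followed: 9.2.1 on AEs leading to discontinuation and 9.2.4 on collection. The follow-up rules and the reference used for relatedness are not aligned with the filter. Non-serious events judged unrelated have no AE entry, so the by-arm summary and the DSMB review depend on individual attribution.

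The likely consequence is modest dilution: in the illustration, power falls from 33% to 26–30% if 80–90% of events pass, and to 17% only if half are lost. These figures rest on assumed event rates, an assumed equal retention in both arms and one event per participant, and they describe a comparison for which the protocol specifies no formal test. Bias between arms is possible in principle but not shown by the document. The change is worth making because it is cheap and the excluded entries cannot be recovered at the analysis stage.

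**What to change.** In section 9.2.4, record all non-serious AEs in the eCRF from randomisation until 30 days after the last visit, and make relatedness a recorded field of each entry. Summarise by arm both all AEs and those judged related. Any limit to possibly related events should apply only to external reporting.

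Then align the neighbouring text. State in 9.2.1 that events leading to discontinuation of study drug are recorded whatever their relatedness, and whether that sentence covers all AEs or only abnormal findings. Use one reference for relatedness in 9.2.4 and 9.2.5, or record relatedness to study medication and to study procedures separately. Let 9.3 and the Grade > 1 rule refer to the same set of recorded AEs. If the sponsor keeps the restriction, the minimum is to exempt events leading to discontinuation from it and to reword 9.2.1, 9.2.5 and 9.3 to match.

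The cost is some additional eCRF entries for 48 participants and a partial reversal of item 8 of the first amendment. No visit or assessment is added. Events already left out before the change may not be retrievable, so the date of the change should be noted in the safety summary.

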Our study participants will be referred to the AMC intervention radiology department for liver biopsy to assess NASH histology severity, pathophysiological pathways and gene expression in liver tissue. As an experienced interventional radiologist will perform the liver biopsy ultrasound-guided, the risk (comprising mostly bleeding from the biopsy site) of complications will be very low (<0.1 %). Moreover, local hemostasis after the procedure will be observed and bleeding disorders or anticoagulant therapy are an exclusion criterion. Based on our previous experience, we might encounter  $\pm 1$  patient with a complication (most likely small bleeding) in our entire study. To date, a liver biopsy is still the gold standard for discerning the severity of NASH and provides the possibility to study pathophysiological pathways and gene expression.

In addition, a multiparametric MRI of the liver and MRI of visceral and subcutaneous fat will be performed with a 3T Philips Ingenia MRI scanner. Participants will be screened for contraindications for MRI prior to inclusion in this study. Participants will be provided with metal free hospital clothing if necessary. The total scan time will be approximately 45 minutes to estimate visceral and subcutaneous adipose tissue depot volume, hepatic and pancreatic fat content, as well as hepatic fibrosis and inflammation.

Last, continuous glucose measurements will be performed at home using portable devices, during a consecutive period of 1 week (7 days) in the week before baseline, week 1, 9, 17 and 25.

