## 3. STUDY DESIGN

### Study visits:

Participants who are foreseen to fulfil the inclusion / exclusion criteria for enrolment into the clinical study will be informed and interviewed. When theoretically eligible for participation, participants are asked to give informed consent in writing prior to any clinical study specific procedures. Both the participant and investigator (or designee) will sign and date the informed consent form. After, a liver biopsy will be performed (unless there is a liver biopsy available obtained < 32 weeks prior to screening) to assess if histopathological inclusion criteria are met.

A MRI of the liver and surrounding area (including pancreas and visceral adipose tissue; as previously specified) will be performed for all eligible participants before the biopsy, unless the biopsy was already performed prior to inclusion.

All eligible participants will visit the study physician 4 times; at baseline, after 8, 16, and 24 week. The study visits will be 8 weeks apart, although a margin of -3 days to +3 days is implemented to take participants schedule and availability into account.. At baseline, blood

and feces, will be collected, a Fibroscan will be made and participants will fill out the SF36.2 and CDLQ-NAFLD quality of life questionnaires. After, participants receive 21 LFMT or placebo capsules to orally ingest. The ingestion of the 21 capsules will be spread over the day to prevent clotting of capsules in the stomach. In addition, for the whole duration of the study participants will daily ingest 2 LFMT capsules (or placebo). At the next visit after 8 weeks blood will be withdrawn, feces will be collected and patients will again ingest 21 LFMT capsules (or placebo). The visit at 16 weeks will be the same as the visit at 8 weeks. The visit at 24 week will be the same as the baseline visit, however, at 24 weeks the visit will also include a liver biopsy. Moreover, patients will hand in fecal samples at baseline, week 2, 8, 10, 16, 18, and 24. Also, continuous glucose measurements will be performed at home using portable devices, during a consecutive period of 1 week (7 days) in the week before baseline, week 1, 9, 17 and 25.

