#### *Screening liver biopsy*

Percutaneous liver biopsies will be performed as a part of screening when individuals are theoretically eligible for participation, unless a liver biopsy has been performed in the previous 36 weeks. A tandem-read by two liver pathologists blinded to any other result will determine if patients will be included in the study.

After the screening is completed, participants will be telephoned with further instructions. Individuals will have a total of one screening and four study visits, and time invested will approximately be 24 hours per person.

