#### 8.6 Follow-up of subjects withdrawn from treatment

Withdrawn patients will be followed for SAEs until 6 months after inclusion.

Participants withdrawn for medical reasons will be followed until the interfering condition has resolved or reached a stable state.

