#### **12.5 Temporary halt and (prematurely) end of study report**

The sponsor will notify the accredited METC and the competent authority of the end of the study within a period of 90 days. The end of the study is defined as the last patient's last visit.

The sponsor will notify the METC immediately of a temporary halt of the study, including the reason of such an action.

In case the study is ended prematurely, the sponsor will notify the accredited METC and the competent authority within 15 days, including the reasons for the premature termination.

Within one year after the end of the study, the investigator/sponsor will submit a final study report with the results of the study, including any publications/abstracts of the study, to the accredited METC and the Competent Authority.

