### 13. STRUCTURED RISK ANALYSIS

Also see the structured risk analysis performed for the SYNCH-study (enclosed).

The present study is considered an intermediate risk study. In summary, the two liver biopsies are the main contributors of risk for participants.

Liver biopsies know a complication rate of approximately 1:1000, with self-limiting bleeding as the main adverse event. We will use experienced personnel to reduce the chance of complications. To date, liver biopsy is still the golden standard in the assessment of progression or reduction of NASH, and there is no alternative. In therapy development for NASH, the American FDA, for example, demands liver biopsy in clinical trials. This study will, however, contribute to the further development and validation of multiparametric MRI as a substitute for biopsy by comparing the two.

To date, FMT procedures have not been associated with (serious) adverse events. Literature concerning the treatment with LFMT capsules reports a lower number of adverse events in comparison to the infusion of FMT via duodenal tube. The most prevalent side effects are mild, self-resolving abdominal pain, nausea, diarrhea, and flatulence (also see paragraph 6.4). Donors will be extensively screened for infectious diseases, rendering the chance of translocation of virulent actors small.

Fructo-oligosaccharides, in addition, are a subgroup of dietary fibers, which are already part of a varied diet. They are safe, well-researched and already over-the-counter available.

Moreover, *A. soehngenii*, *B. animalis*, *subsp. Lactis*, and *A. muciniphila* are commensals of the gut and all deemed safe to administer orally in toxicological studies and studies in humans, with no significant adverse event reported.

Last, we will withdraw blood (5x) and collect feces (7x), patients will complete several questionnaires and keep track of a food diary.

To evaluate and maximize the safety of participants, the study will be monitored by the clinical monitoring center and the DSMB.

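### Non-serious AEs are collected only from randomisation, so those caused by the screening biopsy are missed; the SAE end dates in 8.6, 9.3 and 12.5 also need aligning with 9.2.2 and 9.2.4

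*Protocol*

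**What the plan says.** **AE and SAE windows.** Under 9.2.4, non-serious AEs possibly related to the study "are collected from randomization until 30 days after the last visit (at 24 weeks". SAEs are recorded from signed consent until 30 days after the last investigational product (9.2.4; 9.2.2 likewise gives 30 days after treatment ends).

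**First biopsy.** Section 8.3: "Percutaneous liver biopsies will be performed as a part of screening when individuals are theoretically eligible for participation". Section 3 places it after written consent and waives it if a recent enough biopsy exists. The reading by two pathologists decides inclusion.

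**Second biopsy.** Section 3: "at 24 weeks the visit will also include a liver biopsy". This is the last of the four study visits.

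**Biopsy risk.** Section 13 calls the two biopsies the main contributors of risk, "with self-limiting bleeding as the main adverse event", at about 1 in 1000. The Summary gives a rate below 0.1% and then continues "Based on our previous experience, we might encounter" about one patient with a complication in the whole study.

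**Other SAE limits.** Section 9.3: "SAEs need to be reported till end of study within the Netherlands, as defined in the protocol". Section 12.5: "The end of the study is defined as the last" patient's last visit. Section 8.6: "Withdrawn patients will be followed for SAEs until 6 months after inclusion".

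**The concern.** A self-limiting bleed will usually be non-serious. If collection of non-serious events opens only at randomisation, the rule leaves out the expected complication of the first of the two procedures that the protocol regards as its main hazard. Patients who consent, are biopsied for the study and then fail the histological criteria carry that risk, and their non-serious events are never collected. At stake is the completeness of the trial's safety account, not its efficacy result.

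The end of follow-up raises a second issue. Three sections give an end date for SAE recording or follow-up that can fall before the 30 days after last product required in 9.2.2 and 9.2.4. Site staff cannot follow all of them.

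**Working it through.** No sample size or power figure is involved. The check sets the windows against the order of events, with some side arithmetic.

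**1. Order of events (3, 8.3).** Consent → screening biopsy, unless a recent one exists → tandem read → inclusion and randomisation → visits at weeks 0, 8, 16 and 24, with the second biopsy at week 24.

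**2. Coverage of each biopsy (9.2.4).**

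| | SAEs | Non-serious AEs |
|---|---|---|
| Screening biopsy to randomisation | covered from consent | not covered |
| Biopsied screen failures | covered from consent | never covered |
| Week-24 biopsy and next 30 days | 30 days after last product (9.2.4) | covered |

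For the last row, sections 3 and 8.3 list no visit or call in those 30 days. They do place home glucose monitoring in week 25 and a food diary in the week after study visits; neither is described as a way of asking about AEs.

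**3. Number of biopsies and expected complications.** Inputs: 48 patients (4.4), two biopsies each at most, rate 0.1% (Summary, 11.3, 13).
- Total: 48 × 2 = 96 biopsies. Expected complications 96 × 0.001 = 0.096; P(at least one) = 1 − 0.999^96 = 9.2%.
- First biopsies only: 48 × 0.001 = 0.048; P(at least one) = 1 − 0.999^48 = 4.7%.
- The Summary's other estimate, about one patient in the study, implies 1/96 = 1.04% per biopsy, roughly ten times the stated rate. For the 48 first biopsies that gives 48/96 = 0.5 expected and P(at least one) = 39.5%.

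Both counts are upper bounds for randomised patients, since some bring an earlier biopsy. Biopsied screen failures would add procedures; the protocol gives no number for them.

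**4. SAE end under 9.3 with 12.5.** The end of the study is one date for the whole trial. For the last patient, the last visit is at about day 24 × 7 = 168, while last product plus 30 days is about day 198, a shortfall of about 30 days that begins at the visit with the second biopsy. A patient whose last visit is d days before that date falls short by 30 − d days if d is below 30, and otherwise not at all.

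**5. SAE end under 8.6.** Take six months as about 182 days and inclusion as baseline (an assumption; the term is not defined). A patient whose last dose is on day x needs recording to day x + 30. Section 8.6 ends earlier when x + 30 > 182, that is x > 152.
- Stop on day 30: followed 182 − 30 = 152 days after last dose, well beyond 30.
- Stop on day 160: needed to day 190, so 8 days short.
- Upper limit, day 168: needed to day 198, so 16 days short.

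If inclusion means consent, s days before baseline, the threshold becomes day 152 − s.

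**The case against.** The strongest reply is that little is lost. SAEs run from consent, and 9.2.2 counts any inpatient admission as serious, even a precautionary one, so a bleed that leads to admission is recorded. Haemostasis is observed after the procedure. Patients with a qualifying earlier biopsy have no study biopsy at screening. The screening biopsy precedes randomisation, so the gap cannot favour either arm. All of this stands. It limits the gap to minor, non-admitted events, but those are what the protocol expects.

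A reader might infer more than the documents support:
- *That the second biopsy is also outside the window.* It is inside, with 30 days after it.
- *That there is no contact after week 24.* The text describes none for AEs, but Figure 8 is not shown in the copy at hand, and 9.2.4 uses an undefined abbreviation (EAPV) that may name a further visit. Only the absence of a described contact can be stated.
- *That withdrawn patients are in general followed for less time than completers.* Measured from last dose, most are followed longer. Section 9.2.2 also applies to any participant, so 8.6 could be read as additional follow-up.
- *That safety is ascertained unevenly between LFMT and placebo.* The same rules apply to both blinded arms.
- *That the trial could settle 0.1% against 1%.* With 96 biopsies and perfect capture, zero events has probability 0.999^96 = 91% at 0.1% and (95/96)^96 = 37% at 1.04%. Zero events would leave a 95% upper bound of 1 − 0.05^(1/96), about 3%. A count near zero is also what the stated rate predicts, so it need not result from the windows.

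**Conclusion.** The point holds in a limited form. As written, non-serious complications of the study's screening biopsy are not collected, in randomised patients or in biopsied screen failures. Up to 48 procedures in randomised patients are affected, with between 0.048 and 0.5 expected complications depending on which of the protocol's own figures is used. Neither the arm comparison nor the primary endpoint is affected.

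The week-24 biopsy has a valid window; what is missing from the text is a stated way of collecting events in it. The SAE end dates do conflict, but only for patients finishing within 30 days of the trial's last visit and for those stopping after about day 152, the latter taking inclusion as baseline and six months as 182 days. The mismatch between the two biopsy risk figures is a separate inconsistency in the risk text.

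**What to change.** - In 9.2.4, start collection of procedure-related non-serious AEs at consent, and state that screen failures are included. Name study procedures explicitly, because 9.2.5 rates causality against study medication only.
- State that AEs are asked about by telephone at the end of the existing 30-day window, unless such a contact is already scheduled.
- Reconcile 8.6, 9.3 and 12.5 with 9.2.2 and 9.2.4 so that no patient's SAE recording ends before last product plus 30 days.
- Reconcile the rate below 0.1% per biopsy with the expectation of about one patient in the study; at most 96 biopsies in randomised patients give 0.096 expected at 0.1%.

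The cost is protocol wording, a few more AE entries from screening, and one short call per patient. If 12.5 is aligned by redefining the end of the study, that date moves by about 30 days.
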